### Ethics

This study has been approved by The Queen Elizabeth Hospital (TQEH) Human Research Ethics Committee (Reference number: HREC/17/TQEH/58).

### Study design

This study is a prospective single-blinded randomized controlled trial (RCT) for a period of 6 months. Participants will be randomized 1:1 between the intervention and standard care. The data analysed will be based on intention-to-treat analysis. After receiving informed consent from the participants, baseline measures will be collected. Figure 1 illustrates the study design.

**Fig. 1 Fig1:**
[figure not shown]
CONSORT 2010 Flow Diagram for SMART-MOVE study

### Recruitment

Participants recruited are community-dwelling older people who present to TQEH through the Emergency Department, Acute Medical Unit, Geriatric Evaluation and Management Unit and Geriatrics Medicine Outpatients (including clinics at the Adelaide Geriatrics Training and Research with Aged Care [G-TRAC] Centre). Potential participants are approached by treating clinicians, and if these participants express interest, further contact will be made by one of the research team members to explain the study. Participants will also be recruited from community-based falls prevention programs (i.e. Resthaven Incorporated, Southern Cross). Research personnel will attend the programs and contact telephone number and e-mail will be provided for participants to express their interest. Flyers will be distributed through established community-based organisations for seniors such as Council for the Ageing. This study will also be advertised in newsletters of these organisations. Community talks about sedentary behaviour and falls at various seminars will be provided by the research personnel. Those who attended are provided with a contact telephone number and e-mail to express their interest.

### Participants

Participants will be screened as positive if they are aged over 65 years with a rapid cognitive screen of six and above [36] and scores 4 or higher on the STEADI falls risk self-assessment tool [29]. The STEADI toolkit is a broad, evidence-based resource validated to assess falls risk and individualize fall interventions into clinical practice.

Participants are included if they are screened positive, community-dwelling, can walk independently up to 10 m with or without walking aid, are conversant in English and have scores of 1 or more on the FRAIL screen [37].

Participants are excluded if they are unable to participate in the proposed intervention, have moderate to severe dementia, unable to walk independently up to 10 m with or without walking aid, are in the terminal phase of illness, plans to move out of the metropolitan area within 6 months of the screening clinic visit, plan to be away for more than 2 consecutive weeks during the study intervention period or are participating in another similar physical activity interventional study or programme. There is no specific exclusion criterion in relation to current physical activity levels.

Participants will be screened for eligibility by research personnel and provided with an information pack. The initial screening occurs over a telephone interview. If potential participants are interested, they will inform one of the researchers via telephone or email. Those who express interest will be contacted by a research personnel to have the study described further and their willingness to participate determined. They will be given approximately a week to decide on their participation. If they express their intention to participate, they will attend the study centre (either TQEH or Adelaide G-TRAC Centre) for consent and baseline measurements. When possible, the reasons for declining participation will be recorded. Participants will attend the health centre by their own arranged transport.

### Consent

All participants will provide written consent. Participants will be advised of their right to decline participation and to withdraw at any time without giving any reasons. If they withdraw, research team members will not collect additional personal information from them after the time of their withdrawal. Participants will inform the researchers if they want their personal and clinical information already collected to be discarded or if consent is provided, information already collected be retained and analysed for the study. This will be possible as data will only be analysed after completion of the study.

### Randomisation and blinding

Randomisation and allocation of a participating group to intervention will take place after each participant have provided their consent and completed the baseline assessment. To ensure allocation concealment, the allocation will be determined after baseline data collection using a sealed envelope technique. The randomisation sequence will be computer-generated (https://www.randomizer.org/). We will stratify randomisation by sex, to allow equal numbers of men and women in each group. The research assistants in charge of collecting and entering all outcome data will be blinded to intervention allocation throughout the trial. Participants will be informed not to reveal their group allocation to the research assistants performing the assessments. Additionally, research assistants will be informed not to ask participants which group they are allocated to. Research assistants will be trained to ensure consistency with data collection. The number of participants in whom the research assistants are inadvertently unblinded at follow-up will be recorded.

### Intervention group

The intervention has been reported according to the Template for Intervention Description and Replication (TIDieR) (Table 1) [35]. The intervention group will be:

(a) Presented with the objective information regarding their sedentary levels based on the accelerometer recordings (mean daily sedentary time and step counts, and the sedentary time as a percentage of waking hours, measured over 1 week);

(b) Educated about the benefits of exercise by providing them with written information (i.e. the Choose Health: Be Active booklet);

(c) Set goals to decrease their sedentary time by using two face-to-face health coaching sessions, followed by four fortnightly phone calls; and

(d) Using a pedometer for daily step counts as a motivational tool. Pedometer readings will be entered into a diary. Participants will calculate the mean daily steps over 7 days (as shown by research personnel) and in the following week, participants are encouraged to increase their average daily steps by 200 as a goal.

The face-to-face coaching will occur at weeks 0 and 6 (T0 and T6) of the study.

Table 2 describes the content of the health coaching sessions classified according to the CALO-RE taxonomy of behaviour change techniques [28, 38]. All of the techniques will be used during the face-to-face coaching at week 0 and 6. Review of goals, identification of barriers with problem-solving, use of follow-up prompts and relapse prevention will be discussed during telephone interviews at week 2,4, 8 and 10. Goals will be set according to the SMART (Specific, Measurable, Attainable, Realistic and Time-bound) principles. Each participant will choose six ways to decrease their sedentary time and break up prolonged sitting or lying time from a list of pre-specified behavioural items combined with suggestions of their own (Table 3). For example, the first week, a participant may set a goal of breaking up his reading time every 30 min and then in the third week, this participant will add another goal such as walking once a day in the nearby park. Each goal is intended to increase the upright time gradually. The aim is for one goal to be integrated incrementally every fortnight, so that in the final fortnight, participants would have integrated six goals into their daily routine to reduce sedentary time. Activities that participants are encouraged to engage will involve them being in an upright position instead of sitting or lying. In partnership with the investigator, this tailored intervention will attempt to overcome some of the perceived barriers. Participants will be provided with a diary to record if they attempted or achieved their goals set for that period of time. The diary will be collected at the end of the study.

**Table 2 Tab2:** Content for intervention by session based on the CALO-RE taxonomy of behaviour change techniques

Behaviour change technique	Session 1	Session 2	Session 3	Session 4	Session 5	Session 6
	In person	Telephone	Telephone	In person	Telephone	Telephone
Shaping knowledge about the health consequences of sedentary behaviour	X			X		
Goal-setting (behaviour)	X			X		
Goal-setting (outcome)	X			X		
Feedback on behaviour	X			X		
Action planning	X	X	X	X	X	X
Barrier identification/problem solving	X	X	X	X	X	X
Use of follow-up prompts	X	X	X	X	X	X
Review of goals				X		
Relapse prevention/coping planning		X	X	X	X	X

*CALO-RE* Coventry, Aberdeen and London—Refined

**Table 3 Tab3:** Domains for reduction of sedentary time

Domestic—indoors	Watching television or videos
Domestic—outdoors (e.g., gardening)	Screen-based activities (e.g. computer or tablet)
Transportation	Reading
Recreation	Others

A health coach with medical or nursing background will maintain contact through telephone calls, with participants in the interventional group to monitor progress towards reducing sedentary behaviour and to assist participants to overcome any participation barriers that arise. During the fortnightly telephone contacts, health coaches will also enquire about the circumstance of any falls that participants may have experienced and they will discuss strategies for reducing the risk of future falls. Health coaches will undergo training using written materials prepared by the research team.

A pedometer enhanced with a web-interface, Fitbit Zip™ (San Francisco, CA, USA) will be provided to all intervention group participants to provide feedback on the number of steps achieved daily. These pedometers will be provided as a motivational tool to encourage a reduction in sedentary behaviour. Participants will be encouraged to wear the pedometer during waking hours on a daily basis for the whole 12-week intervention period to record their daily steps and provide feedback and motivation to reduce their sedentary behaviour. Participants will be able to keep the pedometer at the completion of the study.

Participants in the intervention group will also be encouraged to attend falls prevention classes provided through one of the local allied health facilities (http://fallssa.com.au/). The aim of these classes is to help address some of the participants’ risk factors for falls. The participants will pay a small fee to attend these classes. The community aged care service providers will offer these classes. If participants have attended one of these classes in a 12-month period prior to enrolment, they will not be required to repeat these classes. They will be provided with information about what participant should do in the event of a fall (Standing Up to Falls—SA Health).

Goal attainment scale (GAS) is a method for quantifying progress towards defined goals [39, 40]. Three goals to reduce sedentary behaviour will be established at baseline by participants in the interventional group using the GAS with assistance from the health coach. Another three goals will be determined at the end of week 6. Once the goals are agreed upon, the health coach and participant will then predict the GAS outcomes on a five-point scale ranging from − 2 to + 2, where a score of 0 indicates achievement of the set goal, a score of − 1 indicates no change from the baseline level of ability for that goal type, − 2 indicates worse performance than at baseline and + 1 and + 2 indicate ‘somewhat better’ and ‘much better’ performance than the set goal, respectively. Attainment of the agreed goals to reduce sedentary behaviour will be assessed at both six and 12 weeks after participant randomization by a research assistant who is unaware of group assignment. The motivation for change will be evaluated using the Change Questionnaire [41]. Participants’ motivation will be assessed at T0, T6, T12 and T24.

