### Control group

The control group will receive written information about the benefits of being active (i.e. the Choose Health: Be Active booklet) and will be provided with their accelerometer data readings during the one face-to-face meeting they have. Like the intervention group, they will be provided with information about what participant should do in the event of a fall. They will also be encouraged to join a falls prevention class if they have not participated in one in the preceding 12 months. No goals will be set and they will not receive any fortnightly phone calls to minimize any confounding motivational effects that might occur. Therefore, the only addition over and above usual care would be the provision of their baseline status from the first accelerometer assessment.

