### Assessments

Assessment of outcome measures will occur at three time points—baseline (T0), week 12 (T12) and week 24 (T24). Assessments performed at these time points are summarized in Table 4.

**Table 4 Tab4:** Methods and timing of assessing variables in this study

Variables	Measure	When	Time to complete
BMI (weight and height)	Calibrated digital scales and stadiometer	T0, T12, T24	1 min
Cognition	Rapid Cognitive Screen	T0	5 min
Cognition	Trail Making Test	T0, T12, T24	8 min
Mood	Geriatric Depression Screen-Five Item	T0	2 min
Frailty	FRAIL screen	T0	2 min
Personality	10-item personality inventory	T0	3 min
Self-reported physical activity	IPAQ—Elderly	T0, T12, T24	5 min
Self-reported sedentary behaviour	MOST questionnaire	T0, T12, T24	5 min
Social Engagement	Lubben Social Network	T0	2 min
Review of falls episode	History-taking	T0, T6, T12, T24	5 min
Fear of falling	Falls efficacy scale	T0, T12, T24	4 min
Activities of daily living	Katz ADL	T0, T12, T24	5 min
Quality of life	EQ5D	T0, T12, T24	2 min
Nutritional status	Mini-nutritional assessment—short-form	T0, T12, T24	2 min
Gait speed	SPPB	T0, T12, T24	2 min
Grip strength	SPPB	T0, T12, T24	5 min
Balance test	Berg Balance	T0, T12, T24	15–20 min
Appendicular lean muscle mass	Bioelectrical impedance	T0, T12, T24	5 min
Motivation to change	Change Questionnaire	T0, T6, T12, T24	5 min
Goal attainment	Goal Attainment Scale	T0, T6, T12, T24	3–6 min
Sedentary time	Accelerometer	T0, T12, T24	
Step counts	Pedometer	T6, T12, T24	2 min
Pedometer adherence	Pedometer	T6, T12, T24	5 min
Neighbourhood Environment	NEWS	T0	15 min

*ADL* activities of daily living, *BMI* body mass index, *IPAQ* International Physical Activity Questionnaire, *MOST* Measure of Older Adults’ Sedentary Time, *NEWS* Neighbourhood Environment Walkability Scale, *SPPB* Short Performance Physical Battery

Demographic information will be collected at T0. This information includes date of birth (age), ethnicity, living arrangement, comorbid conditions and medication use. The Charlson comorbidity index (CCI) will be applied to measure the burden of disease and thus enable confounder adjustment of the results [43]. The index is based on 22 clinical conditions. Each condition is given an associated weight (1, 2, 3 and 6) according to the gravity of the disease.

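### Goals exist only in the intervention arm, so the goal-attainment rater cannot be blinded as stated, and nothing keeps that rater apart from the blinded follow-up assessments

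*Protocol article*

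**What the plan says.** All references are to the protocol article.

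- **Who sets goals.** Intervention group: "Three goals to reduce sedentary behaviour will be established at baseline by participants in the interventional group using the GAS"; three more are set at week 6. Control group: "No goals will be set and they will not receive any fortnightly phone calls".
- **Who rates them.** Intervention group: attainment is assessed at "six and 12 weeks after participant randomization by a research assistant who is unaware of group assignment".
- **General blinding claim.** Randomisation and blinding: "The research assistants in charge of collecting and entering all outcome data will be blinded to intervention allocation throughout the trial". The safeguards are that participants are told not to disclose their arm, assistants are told not to ask, and inadvertent unblinding at follow-up is counted.
- **Pedometer.** Intervention group: the device "will be provided to all intervention group participants to provide feedback on the number of steps achieved daily". Control group: "the only addition over and above usual care would be the provision of their baseline status from the first accelerometer assessment".
- **Schedule.** Table 4 lists goal attainment at T0, T6, T12 and T24, and step counts and "Pedometer adherence" at T6, T12 and T24. They share one table with gait speed, fear of falling and falls history. The table has no column for who collects each item.
- **Acknowledged limitation.** The Discussion concedes imperfect assessor blinding, but only through participants letting their allocation slip.

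**The concern.** A rating of agreed goals can be made only for someone who has agreed goals, and in this trial that means the intervention arm. The task itself discloses the allocation, so a blinded rater of goal attainment is not possible.

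Two things are at stake. First, goal attainment is outcome data. The Aims set a target that 70% of intervention participants achieve at least three goals, and completion of goals is how adherence, a primary feasibility indicator, is judged. A report that repeated the protocol's wording would claim blinding for a measure that cannot have it. Second, assessor blinding is the only blinding that this single-blinded trial describes. If the person who rates goals also measures the between-arm outcomes, that protection is lost where the assessor can influence the result.

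**Working it through.** No figure in the plan bears on this point, so the check sets the statements side by side.

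1. **Goal attainment.** Goals are set in the intervention arm (Intervention group) and none are set for controls (Control group). Having goals to rate therefore identifies the arm. The rater described in the Intervention group section cannot exist.

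2. **The general claim.** Randomisation and blinding covers all outcome data for the whole trial. Goal completion feeds a primary feasibility outcome (Primary outcomes, Feasibility) and the 70% target (Aims). With 40 planned in the arm and all of them rated, that target is 0.70 × 40 = 28 participants. Goal attainment thus falls within the claim, and the claim fails for at least this measure.

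3. **Do the safeguards cover it?** The instructions not to disclose or ask, the count of inadvertent unblinding and the limitation in the Discussion all concern accidental disclosure. Unblinding through a scheduled rating is neither accidental nor caused by the participant. The planned count is not designed to capture it.

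4. **Does it spread to other outcomes?** This depends on who does what, which the article does not say.
   - If goal raters do no other assessments, no other outcome is affected.
   - If the same assistants rate goals and carry out the T12 and T24 assessments, the intervention participants are identified by having goals and the controls by having none. At most, 40 + 40 = 80 participants would be assessed with the arm known.
   - The article provides no separation of staff, forms or order within a visit, so the second case is not excluded.

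5. **Which outcomes would suffer?** Secondary outcomes lists self-reported sedentary time, fear of falling, gait speed, and fallers and falls. Gait speed, a 6-m walk, is the one clearly measured by an assessor. Falls are self-reported, but Table 4 obtains them by history-taking, so the questioning matters. The two questionnaires are answered by participants who know their arm, so assessor blinding protects them little in any case. ActivPAL sedentary time is recorded by a device and is little affected.

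6. **Pedometer.** The Intervention group and Control group sections place it in the intervention arm. Table 1, however, lists it among what participants receive without naming an arm, although it does limit the goal booklet to the intervention group. Statistical analyses also plans a between-group t test that includes days of pedometer wear. If the device is intervention-only and blinded assistants collect its data, step 1 applies to it as well.

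7. **Timing.** The Intervention group section rates goals at weeks 6 and 12; Table 4 adds T24. The two do not agree.

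**The case against.** The strongest reply is that only the goal-attainment statement is shown to be impossible. A reader might infer that the schedule guarantees unblinding of every assessor-rated outcome. The documents do not support that. Table 4 names no collector, nothing says that the goal rater also measures gait speed, and the article speaks of several research assistants. Pedometer readings go into a participant diary and the device has a web interface, so a blinded assistant need not handle them. This stands, and the wider effect is therefore stated only as conditional.

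A reader might also take it as settled that controls get no pedometer. The main text points that way, but Table 1 and the planned t test leave it unclear.

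Nor should the harm be stretched. Berg balance, grip strength and the Trail Making Test appear in Table 4 but are not among the named primary or secondary outcomes, and device-measured sedentary time is largely protected.

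Finally, the protocol already admits that blinding may be imperfect. That shows candour, but the admission concerns inadvertent disclosure and does not resolve a rating that reveals the arm by its nature.

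**Conclusion.** The protocol is wrong as written on one measure. Goal attainment cannot be rated by someone blinded to arm, and the promise of blinded collection of all outcome data cannot hold for it. This follows from the text alone and applies to every goal rating in the 40 planned intervention participants.

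Loss of blinding for other outcomes is possible but not demonstrated. It ranges from none to all 80 participants and rests on the assumption that the same assistants do both tasks. Where it occurred, it would matter chiefly for gait speed and falls history. The pedometer part rests on two further assumptions: that only the intervention arm has the device and that blinded assistants collect its data.

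This is a should-fix. It is a clear contradiction with a cheap remedy, in a feasibility trial whose sedentary-time outcome is measured by a device.

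**What to change.** 1. Remove the description of the goal-attainment rater as blinded.
2. State that goal attainment, pedometer data and diaries are collected on separate forms by existing personnel who perform no blinded T12 or T24 assessments and did not coach that participant. Table 1 names two people delivering the intervention, so the other coach could do this; alternatively, one research assistant could be designated as unblinded. A participant's own coach should not score the goals, because the coach helped to set them and the scores feed the 70% feasibility target.
3. Mark these rows of Table 4 as intervention arm only, unblinded.
4. Limit the claim under Randomisation and blinding to the outcomes compared between arms.
5. Reconcile the T24 goal-attainment entry in Table 4 with the six- and 12-week timing in the text.
6. Make Table 1 and the planned t test of pedometer wear consistent with the sections that give the pedometer to the intervention arm, or state otherwise.

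The cost is a reassignment of forms among existing staff, with no added participants or visits. If an assistant is designated as unblinded, that person is no longer available for blinded assessments. Goal ratings become openly unblinded, which is unavoidable for a measure that exists in one arm only.
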